**12.3 Sensitivity analysis**

In addition, per-protocol analysis and as-treated analysis with GLMMs will be performed to assess the effect of contamination.

**12.4 Missing value**

For potential missing data, GLMM allow data from completed survey to be retained for analysis. A complete-case analysis will be used if an outcome variable miss for <15% of participants. Otherwise, sensitivity analysis using multiple imputations will be conducted to assess the robustness of the missing data.

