**10. Sample size calculation**

The sample size was guided by a Gunn et al. [39]. The primary objective is to compare ART medication adherence at 6 months post allocation between the intervention arm and the control arm. The calculation was based on planned subgroup analysis, for that sample size would need to be larger to observe differences between study arms within strata than combined. Based on a previous SMS intervention in China [26], we calculated the sample size to detect a mean difference of 0.15 in proportions of achieving optimal ART adherence for text message subgroup. Due to no preliminary data, we hypothesized the difference will be no less than 0.15 for the instant message subgroup and instant message plus social media subgroup because participants in these two groups will receive consistent interventions and more incentives (cumulative clock-punching incentive), and consequently may have larger potential for adherence improvement.

Therefore, assuming a mean difference of 0.15 in proportions of achieving optimal adherence, two-sided alpha=0.05, 80% power and 20% loss to follow up, the sample size is 190 for text message subgroup. According to our pilot survey in another infectious disease hospital of Shandong Province, about two-thirds of PLWH are willing to choose instant message, and the others use text message or phone. Consequently, we anticipated that one-third of participants would choose text message in this study and extrapolated the total sample size was 570. The sample size calculation is conducted by PASS 15.

Due to the nature of the design, we cannot ensure participants choosing each of the three digital strategies in the anticipated proportion. And due to the limitation of cost and timeline, we will end up recruiting participants until reaching the total sample size (n=570) instead of satisfying the sample sizes of all three subgroups (each group n=190).

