**12.2 Primary analysis**

The primary analysis will be performed on an intention-to-treat analysis utilizing generalized linear mixed models (GLMMs) to evaluate the effect of the differentiated digital intervention on the primary and secondary outcomes, which will include intervention status as fixed effects and individual participants with multiple measurements as random effects. The GLMMs will adjust for the baseline outcome measures (where appropriate), stratification factors (i.e. text message, instant message, instant message plus social media group), and time (baseline, 3 months and 6 months). Baseline variables significantly associated with the outcomes and found to be imbalanced between intervention arm and control arm will also be considered for adjustment in the regression models. The risk ratio (RR) or mean difference (MD) of the outcomes between study arms will be reported as estimated intervention effects with 95% confidence intervals and two-sided P values.

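### A 15% missing-data cut-off pooled over arms sets an unclear complete-case rule and gates the only missing-data sensitivity analysis, so differential loss below it goes unexamined

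*Protocol*

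**What the plan says.** Three statements in the protocol bear on this.

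- Section 12.2 sets the main analysis: "The primary analysis will be performed on an intention-to-treat analysis". It uses generalized linear mixed models with a participant random effect and with baseline, 3 and 6 months as time points.
- Section 12.4 opens with the model's handling of partial data: "For potential missing data, GLMM allow data from completed survey to be retained for analysis". It continues: "A complete-case analysis will be used if an outcome variable miss for <15% of participants". It ends: "Otherwise, sensitivity analysis using multiple imputations will be conducted to assess the robustness of the missing data".
- Section 10 sizes the text message subgroup with "80% power and 20% loss to follow up", and the total of 570 is extrapolated from that subgroup.

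Complete-case is not defined. The 15% is a share of participants for each outcome variable, and neither arm nor visit is mentioned. No imputation assumption is stated. The other sensitivity analyses, in 12.3, have a different purpose: "per-protocol analysis and as-treated analysis with GLMMs will be performed to assess the effect of contamination".

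**The concern.** There are two problems in one short section.

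First, the rule does not say clearly who is analysed. A participant seen at 3 months but not at 6 months contributes to a mixed model fitted to all records. In a complete-case analysis as usually understood, he is dropped. Section 12.4 points both ways, and the choice would depend on a share known only after follow-up.

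Second, the cut-off decides whether missing data are examined at all. What biases a comparison between arms is loss that is linked to the outcome and differs by arm. An overall share shows neither. Both are plausible here. The outcome is self-reported adherence over the past month (9.1). Participants are not blinded to how they receive the service (7). The clock-punching reward appears only in the description of the intervention (8.2) and not under control (8.4), so engagement with the study may differ by arm. At stake is a primary result that could be partly or wholly an artefact of who returned the 6-month questionnaire, with nothing in the plan to show it.

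**Working it through.** **The plan's own figure.** The difference is 0.15, with two-sided alpha 0.05, 80% power, 20% loss and 1:1 allocation. The control rate is not given. Assuming 0.80 against 0.95 and pooled variance:

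n per arm = [1.96·√(2·0.875·0.125) + 0.8416·√(0.80·0.20 + 0.95·0.05)]² / 0.15² = (0.917 + 0.383)² / 0.0225 ≈ 75.1, so 76.

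2·76 = 152, and 152/0.80 = 190. The stated 190 reproduces at that assumed control rate, and 3·190 = 570. Other control rates give other totals (0.75 against 0.90 gives 250). The sample size is not in dispute. The step matters because it shows that the 20% loss is built into the plan.

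**Which branch applies.** 15% of 570 is 85.5, so 85 or fewer missing falls in the complete-case branch. The planned 20% is 114, which falls in the imputation branch.

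**How many a literal complete-case rule could drop.** Suppose 14% are missing at each follow-up and anyone with a missing visit is excluded. The share excluded is 14% if the same people miss both visits, 1 − 0.86² = 26% if misses are independent, and 28% if they do not overlap.

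**Differential loss under the cut-off.** Assumptions (not document values): 285 per arm, no true effect, true optimal rate p of 0.65 or 0.72, all missing suboptimal, and loss m in an arm. Completers then show p/(1 − m). The last column is the chance that a two-sided 5% Wald comparison of completer proportions rejects.

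| Loss control / intervention (overall 14%) | Completers, p = 0.65 | Completers, p = 0.72 | Spurious difference | Type I error |
|---|---|---|---|---|
| 14% / 14% | 0.756 / 0.756 | 0.837 / 0.837 | 0 | 0.05 |
| 12% / 16% | 0.739 / 0.774 | 0.818 / 0.857 | 0.035 to 0.039 | 0.15 to 0.22 |
| 10% / 18% | 0.722 / 0.793 | 0.800 / 0.878 | 0.070 to 0.078 | 0.45 to 0.66 |
| 7% / 21% | 0.699 / 0.823 | 0.774 / 0.911 | 0.124 to 0.137 | 0.90 to 0.99 |

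For 10%/18%: 0.10·285 + 0.18·285 = 79.8, and 79.8/570 = 14%, so no imputation is triggered. If the control arm loses more, the sign reverses.

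With a real effect and equal loss (0.65 against 0.80, 14% each), completers show 0.756 against 0.930. The difference rises to 0.174 but the risk ratio stays at 1.231, so unequal loss is what matters for the effect measure named in 12.2.

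**What a missing-as-suboptimal check would reveal.** Suppose completers show 0.80 against 0.95. Counting the missing as suboptimal multiplies each rate by (1 − m):

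- 14%/14%: 0.688 against 0.817, difference 0.129.
- 10%/18%: 0.720 against 0.779, difference 0.059.
- 7%/21%: 0.744 against 0.750, difference 0.006 (unrounded: 0.7505 − 0.744 = 0.0065).

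**At the planned 20%.** With loss of 15% in control and 25% in intervention (20% overall), no true effect and the same assumptions, completers show 0.765 against 0.867 (p = 0.65) or 0.847 against 0.960 (p = 0.72), a spurious difference of 0.102 to 0.113. Here imputation is done. A standard missing-at-random version fills gaps from similar observed participants, so it would largely return the completers' contrast.

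**The case against.** The strongest reply is that complete-case here means only that nothing is imputed. The sentence on imputation begins as the alternative to it, and imputation is labelled a sensitivity analysis. On that reading the mixed model of 12.2 is fitted to observed records on both sides of 15%, nothing switches, and intention-to-treat is intact. This reading is tenable. A reader might therefore go too far in calling the section a proven contradiction or a breach of intention-to-treat. What stands is that the text allows two analysis sets for the primary outcome.

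A second reply is that imputation models and delta shifts often belong in an analysis plan, which is not shown. That also has force. A reader might infer that the planned imputation cannot detect drop-out linked to non-adherence. The protocol does not support that, because it states no imputation assumption and imputation can be done under missing not at random. It is fair to say only that the usual missing-at-random version would not test for it and that the protocol commits to no other. The 15% gate, by contrast, is stated in the protocol and is not a detail left open.

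Third, the plan expects 20% loss, so the complete-case branch is not the expected one for the survey outcomes. That limits the reach of the cut-off. Payment for each completed questionnaire in both arms (6.3) may also hold loss down and keep it balanced.

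Two further inferences should be resisted. Worst-case bounds at 14.9% missing put an observed 15-point difference anywhere from 0.851·0.15 − 0.149 = −2 points to 0.851·0.15 + 0.149 = +28 points. They need all the missing in one arm to be optimal and all in the other suboptimal, which is not the mechanism feared here. With all the missing suboptimal in both arms the figure is 0.851·0.15 = 12.8 points. And the match between a 15% cut-off and a 15-point effect is a coincidence between two different quantities.

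**Conclusion.** The point holds as a defect in a stated rule. Section 12.4 leaves the analysis set for the primary outcome ambiguous, and it makes the only missing-data sensitivity analysis depend on an overall share that cannot show imbalance between arms.

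The size depends on assumptions. If the missing are all suboptimal and there is no true effect, 10%/18% loss gives a spurious 7 to 8 points, about half the planned 15. At 12%/16% it is 3.5 to 3.9 points, and at equal loss it is zero. All-suboptimal is the extreme of that mechanism, so weaker links give smaller bias.

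The figures describe a comparison of 6-month completers. A mixed model on all records recovers what 3-month answers predict, but not drop-out that depends on unseen 6-month adherence. The illustration therefore argues mainly against the gate. The case against complete-case analysis itself is the needless loss of observed records. This should be corrected, but it does not show that the trial's result will be biased.

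**What to change.** In section 12.4:

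1. Delete the 15% rule and the term complete-case.
2. State that the mixed model of 12.2 is fitted to all observed records, whatever the missing share.
3. Report missingness by arm and visit.
4. Whatever the missing share, report two sensitivity analyses for the 6-month primary outcome: missing counted as suboptimal adherence, and multiple imputation with delta shifts set separately by arm and stepped until the conclusion changes (tipping point).

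The cost is a change of wording and a few more analysis runs, with no new data. The downside is that the result may look less favourable. Missing-as-suboptimal is itself a strong assumption and should be presented as one end of a range, with the tipping point showing how far from the main analysis the conclusion survives.

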**12.5 Subgroup analysis**

Subgroup analysis by different digital strategies will be carried out to compare the primary and secondary outcomes between the study arms within each of the three strata. As we mentioned before, the sample size may not be sufficient for all three subgroups. But based on the preliminary data and sample size calculation, we can ensure sufficient power in total and at least one of the three intervention subgroups.

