**2. Summary**

**Background:** The antiretroviral therapy (ART) requires a high level of adherence to ensure its effectiveness but adherence is suboptimal in many settings. Digital interventions have shown significant potential to improve ART adherence but there have been few ART interventions in China.

**Purpose:** This purpose of this study is to evaluate whether a differentiated digital intervention can improve ART adherence among men who have sex with men (MSM) living with HIV in China.

**Design:** This is a pragmatic randomized controlled trial (RCT) with two parallel arms including a baseline survey and two follow-ups with 3 months interval.

**Sites:** An infectious disease hospital (designated ART delivery site) in Jinan, Shandong Province of China

**Study populations and eligibility**: A total of 570 participants will be recruited. Eligibility criteria include MSM living with HIV who are currently on ART in the hospital, 18 years old or above, and willing to choose one of the three digital strategies (text message, only instant message or instant message plus social media group).

**Randomization**: Participants will be assigned to the intervention arm or the control arm through stratified block randomization (stratification=3, block sizes=4).

**Interventions**: The interventions include health messaging, medication reminders, peer education and online group discussion. Intervention contents are consistent but the ways of intervention delivery will be adapted based on different digital strategies.

**Study outcomes**: The primary outcome is ART adherence within the previous month. Secondary outcomes include CD4 T-cell counts, HIV detectable viral load, HIV treatment adherence self-efficacy and quality of life.

**Trial registration:** ChiCTR2000041282, retrospectively registered on 23 December 2020.

**Keywords:** Antiretroviral therapy adherence; Digital intervention; Social media; Men who have sex with men; Randomized controlled trial; China

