**3.2 Objectives**

**Primary objective**: To determine if the differentiated digital intervention can improve ART adherence among MSM living with HIV at 6 months compared to the control arm.

**Hypotheses 1**: The differentiated digital intervention is superior in improving ART adherence compared to the control arm.

**Secondary objectives**: To determine (1) whether CD4 T-cell counts, HIV viral suppression, HIV treatment adherence self-efficacy and quality of life differ between the intervention arm and the control arm at 6 months; (2) whether the outcomes (i.e. ART adherence, CD4 T-cell counts, HIV viral suppression, HIV treatment self-efficacy and quality of life) differ between the two study arms within each of the three subgroups (i.e. text message subgroup, instant message subgroup, and instant message plus social media subgroup)

**Hypotheses 2**: The differentiated digital intervention is superior in improving CD4 T-cell counts, HIV viral suppression, HIV treatment adherence self-efficacy and quality of life. Text message-based intervention, instant message-based intervention, and instant message plus social media intervention are superior in improving the health outcomes.

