A customized WeChat mini-program entitled “U=U” (Undetectable=Untransmittable) is developed to remind participants to take medications on time and also provide them the opportunity of online clock-punching after taking medication. WeChat mini-program, a revolutionary lightweight “APP” without the need of downloading, can significantly improve accessibility and convenience [35]. First, the research staff will send QR codes and manual of the mini-program to participants via WeChat. Those who are interested in this service can scan QR codes to authorize the login of their WeChat accounts. After that, research staff can identify them from the management platform of this mini-program and type in their ART medication information (i.e. prescribed medication time and frequency of daily medication-taking) collected from baseline questionnaire. Then the participants can enter the user interface (UI) of the mini-program (Figure S5) to complete online clock-punching. The valid time of clock-punching is limited to one hour after prescribed medication time. If the participants try to punch the clock beyond the valid time, a prompt window “Sorry, invalid clock-punching for timeout” will pop up. The participants will be awarded about 4.48 USD if they complete 30-days uninterrupted clock-punching and the reward is cumulative. A clock-punching calendar recording each participant’s own valid clock-punching dates is also available in UI of the WeChat mini-program (Figure 4). Also, participants who need daily medication reminders can receive the service delivered by this mini-program three minutes ahead of their prescribed dose-timing.

[figure not shown]

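### The three strategy-specific hypotheses are tested stratum by stratum with no planned arm-by-strategy contrast, so read side by side, equally effective strategies can easily look different.

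*Protocol*

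**What the plan says.** Secondary objective (2) in Section 3.2 asks whether the arms differ within each of the three strategy subgroups on five outcomes: adherence, CD4 count, viral suppression, self-efficacy and quality of life. Hypothesis 2 then asserts that "Text message-based intervention, instant message-based intervention, and instant message plus social media intervention are superior in improving the health outcomes".

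The method in Section 12.5 is "to compare the primary and secondary outcomes between the study arms within each of the three strata". Section 12.2 describes a GLMM with an arm effect, adjusted for strategy, time and baseline outcome. Strategy is there as an adjustment factor; no arm-by-strategy term is named.

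These strata also drive the sample size. Section 10 states that "The calculation was based on planned subgroup analysis". It is done "assuming a mean difference of 0.15 in proportions of achieving optimal adherence", with "two-sided alpha=0.05, 80% power and 20% loss to follow up", and concludes that "the sample size is 190 for text message subgroup". The total of 570 is three times that figure. Sections 10 and 12.5 both concede that stratum sizes are not guaranteed and that some strata may be too small.

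**The concern.** The plan gives three separate answers, one per strategy, and nothing that compares them. The protocol nevertheless invites the comparison. Section 10 argues that the two WeChat strata have more room for improvement than the text message stratum. Section 8.3 sets up the QQ group to learn whether interaction among participants helps, and that can only be seen by setting the third stratum's effect against the second's.

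A significant result in one stratum and a non-significant one in another is not evidence that the effects differ. With no planned contrast, a reader has only the three separate results to go on and may take such a pattern as a finding about strategies.

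A distinct issue is that adherence is tested for superiority three times at the full 0.05, which raises the chance that some stratum is declared positive when no strategy works.

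**Working it through.** **Inputs.** From Section 10: difference 0.15, two-sided alpha 0.05, power 80%, loss 20%, 190 per stratum. From Section 7: 1:1 allocation. The control rate behind the sample size is not stated. I assume 0.80, because it reproduces 190, and vary it. Section 3.1 gives background rates of 81.1% and 68.3%, but for at least 95% adherence, which is not the primary outcome definition in Section 9.1.

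**The plan's own figure.** n per arm = [z(0.975)·√(2p̄(1−p̄)) + z(0.80)·√(p1(1−p1) + p2(1−p2))]² / d².
- For 0.80 versus 0.95, p̄ = 0.875: [1.960·√0.21875 + 0.842·√0.2075]² / 0.0225 = 75.1, so 76 per arm; 152/0.8 = **190**.
- The same formula gives 175 with a control rate of 0.811 and 318 with 0.683.

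**Mixed pattern when all three strategies work equally.** The strata are independent. With power π in each, P(mixed) = 1 − π³ − (1−π)³.
- Design value, π = 0.80: 1 − 0.512 − 0.008 = **48.0%**.
- Control 0.683, 76 evaluable per arm, π = 0.58: 1 − 0.195 − 0.074 = **73.1%**.

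Other control rates, 76 per arm:

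| Control rate | Power per stratum | P(mixed) |
|---|---|---|
| 0.80 | 80.5% | 47.2% |
| 0.75 | 68.5% | 64.7% |
| 0.60 | 50.6% | 75.0% |
| 0.50 | 46.4% | 74.6% |

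A binomial simulation gives 41.9% at control 0.80, so the range at design power is about 42–48%. With strata of 190, 285 and 95 (illustrative), P(mixed) is 61.3% at control 0.80 and 78.7% at 0.683.

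**What a direct contrast does.** In the same simulation (100,000 runs, control 0.60, 0.683 or 0.80, true difference 0.15 in every stratum), a 2-df test that the three risk differences are equal rejects about 5.4% of the time. Its weakness is power: if one strategy has no effect and the other two have 0.15, it rejects in only 28–42% of runs.

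**False positives when no strategy works.** P(at least one of three significant) = 1 − 0.95³ = **14.3%** for adherence. This counts either direction; in favour of the intervention only, it is 1 − 0.975³ = 7.3%.

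**Does multiplicity control cure the mixed pattern?** No. Simulating three independent strata with Holm, P(mixed) goes from 48% to 47% at 80% power, and from 73% to 62% at 58% power. The latter drop arises mainly because the chance that no stratum is significant rises from 7% to 21%. A plain split of alpha (0.0167 each, control 0.80) lowers power per stratum from 80.5% to 66.0% and raises P(mixed) to 1 − 0.66³ − 0.34³ = 67%. The two problems need separate remedies.

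**The case against.** The strongest reply is that the protocol never says it will rank strategies. Objective (2) asks about arms within strata, and Section 12.5 plans just that. Because randomisation is stratified by the chosen strategy, each comparison is unbiased despite self-selection. An interaction term or a multiplicity rule could also sit in a statistical analysis plan that is not shown. Most of this stands: the 48% and 73% describe what happens if the results are set side by side, not an analysis the protocol prescribes. What remains is that the protocol itself fixes the three superiority hypotheses, the within-stratum method and the unadjusted 0.05 behind 190, and motivates comparison between strategies in Sections 8.3 and 10.

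Three stronger readings are tempting and not supported:
- A reader might count 15 tests (five outcomes by three strata) at 5% and quote 1 − 0.95¹⁵ = 53.7%. The protocol states 0.05 only in the adherence sample size, and the outcomes are correlated, so this is at most an upper bound on an inferred rule.
- A reader might say the second objective would be decided by p-values alone. Section 12.2 reports effects with 95% confidence intervals as well.
- A reader might treat the summary's "Intervention contents are consistent but the ways of intervention delivery will be adapted based on different digital strategies" as concealing a difference in content, since Section 8.2 says "The participants will be awarded about 4.48 USD if they complete 30-days uninterrupted clock-punching and the reward is cumulative" and text message participants are offered nothing similar. The summary is loosely worded, but Section 10 openly cites the extra incentive and Section 8.3 describes the group. It bears on interpretation only: a difference between strata could not be put down to delivery mode alone.

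**Conclusion.** The point holds as a cheap improvement to the secondary, strategy-specific analysis. The plan lacks the one estimate that would show whether strategies differ. Without it, three equally effective strategies would show a mixed pattern about 48% of the time at 80% power per stratum, and more often if power is lower or strata are unequal. The 73% figure rests on a control rate borrowed from a different adherence definition and should be read as illustrative. Separately, the chance of at least one falsely significant stratum for adherence is 14.3% under no effect anywhere.

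A reader might infer that missing multiplicity control makes equal strategies look different. It does not; that comes from the missing contrast. Nor is the main result in doubt: the primary objective is a single overall comparison and is unaffected.

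**What to change.** In Section 12.5:
1. Estimate the stratum effects from one GLMM with an arm-by-strategy interaction at 6 months. Report the three effects and their differences with 95% confidence intervals, together with the interaction test.
2. State that no strategy will be called better or worse than another on the basis of within-stratum p-values.
3. As a separate matter, apply Holm over the three strata for adherence if stratum-specific superiority is to be claimed, and label stratum results on the secondary outcomes exploratory.

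The cost is one model term and a few sentences. There are two drawbacks. The interaction test has low power (28–42% in the scenario above), so a non-significant result must not be read as equality; the estimated differences and their intervals should carry the message. Holm makes the stratum p-values stricter, so fewer stratum claims would succeed at the planned 190.
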